### Aims

The aim of this study is to test the efficacy of Seeking Safety versus standard CBT in a Dutch sample of outpatient SUD patients who have experienced at least one traumatic event. As the population under study consists of patients in treatment for substance use, the primary outcome measure is substance use severity. Secondary outcome measures are PTSD and trauma symptoms, coping skills, functioning, and cognitions. We will also assess drop-out and satisfaction.

A second aim of the study is to perform a cost-effectiveness analysis to compare the two treatments.

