### Sample size calculation

The sample size for this study is calculated using a significance level of 95% (p < 0.05), a power of 80% and the same number of patients in the intervention and control group (ratio = 1).

Primary outcome variable is substance use severity as measured with the EuropASI. In recent studies, conducted within the same institution [34] but with a population of inpatients, a mean baseline score of 5.2 was found for the alcohol domain and 4.0 for the drugs domain. We expect the mean baseline scores for the outpatients to be somewhat lower, however not considerably. For comparison of baseline scores on the EuropASI, see [22,23]. For practical reasons we are using the mean of both domains (alcohol and drugs) for the sample size calculation. Thus, the mean score for substance use severity will be somewhat lower than (5.2 + 4.0)/2 = 4.6 with a standard deviation of 2.7. For this sample size calculation we will use a baseline score of 4.0 with the same standard deviation. We expect the substance use severity to improve with 60% [23] to 1.6 (SD = 2.0) at end-of-treatment for the intervention group and 2.8 (SD = 2.0) for the control group. We used PS – Power and Sample Size Calculation to calculate the sample size, which resulted in a sample size of 45 patients in each group. Drop-out rates for this treatment are available for the past years from a management information system and are estimated around 20%. This drop-out rate may seem low compared to the numbers that are known from previous studies in SUD patients. However, we will use this percentage to calculate the number of patients that are needed, but will perform an analysis on drop-out halfway through the study. When the drop-out rates turn out to be higher than expected, an amendment will be proposed to the medical ethical committee to continue including patients for an extended period of time. Because of the calculated drop-out rate, an extra 9 participants will be included in both the intervention and the control group, yielding a total of 108 participants for the randomized controlled trial. Based on treatment entry numbers from previous years, approximately two years will be needed to include all patients. Furthermore, this number of patients seems plausible considering sample sizes in previous studies that show similarity in design [21,22].

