### Cost-effectiveness analysis

To make a comparison between the two treatments, the cost of these treatments (total costs of staff and materials) will be related to the benefits of the treatment by performing a cost-effectiveness analysis. A cost-effectiveness analysis requires a numerical estimate of the magnitude of the effects of an intervention on health outcomes. The primary outcome measure of this study will be used for this purpose. Cost will be divided by effects to calculate the cost-effectiveness ratio (C/E). The statistics of interest in the economic evaluation of health care interventions is the incremental cost-effectiveness ratio, which is defined as the difference in cost between Seeking Safety and CBT. To quantify uncertainty in the estimated incremental cost-effectiveness ratio, confidence intervals will be calculated. In addition, a special variant of economic analysis is planned, i.e., cost-utility analysis, to incorporate the preferences (utilities) of the participants considering their own health status at the start of treatment and after follow-up. Based on these preferences combined with life expectancy figures, calculation of so-called QALYs is applicable. A general measure to express the benefits of the two different treatment strategies will be calculated by subtracting the number of quality-adjusted life years computed after follow-up from the number of QALYs computed at baseline. Subsequently, quality-adjusted life years can be combined with the cost of each treatment strategy to arrive at the cost per QALY gained [48,50].

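### Cost per QALY rests on before-after change and each strategy's own cost, and the ICER is defined without an effect difference; neither is written as an incremental ratio between randomised arms

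*Protocol article*

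**What the plan says.** The Aims section of the protocol article sets the purpose: "A second aim of the study is to perform a cost-effectiveness analysis to compare the two treatments". The Cost-effectiveness analysis section then describes two analyses.

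- **EuropASI-based analysis.** It begins with an average ratio: "Cost will be divided by effects to calculate the cost-effectiveness ratio (C/E"). It goes on to name the "incremental cost-effectiveness ratio, which is defined as the difference in cost between Seeking Safety and CBT" as the quantity that matters, and adds: "To quantify uncertainty in the estimated incremental cost-effectiveness ratio, confidence intervals will be calculated".
- **Cost-utility analysis.** This is introduced as an additional variant with its own construction. The benefit is found by "subtracting the number of quality-adjusted life years computed after follow-up from the number of QALYs computed at baseline", and then "quality-adjusted life years can be combined with the cost of each treatment strategy to arrive at the cost per QALY gained".

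Nowhere in the section is a difference between the arms in effect or in QALYs written down. The interval is promised for the ICER, and none is mentioned for the cost per QALY.

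**The concern.** The decision that this analysis is meant to inform is whether to offer Seeking Safety in place of CBT. That needs the extra cost per extra unit of benefit, estimated between randomised arms. A therapy's cost divided by its own before-after change answers a different question and credits that therapy with whatever would have changed anyway.

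Shared change is plausible in this trial. The Inclusion criteria require active use in the previous 30 days and a SRIP score of at least 40, and the Discussion accepts that some reported symptoms may come from substance use or withdrawal. Patients selected in this way may improve on average in both arms. Randomisation removes such improvement from a difference between arms, but not from two separate ratios.

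The ICER has a different fault. Defined as a cost difference alone, it is not a ratio and does not depend on the treatment effect at all.

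**Working it through.** **Inputs.** The Cost-effectiveness analysis section gives no cost, utility, QALY or threshold figure, so it has no result to reproduce. All cost, QALY and threshold figures below are assumed illustrations. The only trial figures used are from the Sample size calculation: "we will use a baseline score of 4.0 with the same standard deviation", improving "to 1.6 (SD = 2.0) at end-of-treatment for the intervention group and 2.8 (SD = 2.0) for the control group". Those means imply a between-arm difference of 2.8 - 1.6 = 1.2. With SD 2.0, two-sided 5% and 80% power, a t-test needs 44.6, rounded up to the stated 45 per group. This confirms that 1.2 is the planned contrast and has no other bearing here.

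**Step 1: formulas.**
- Average ratio for an arm = C_arm / E_arm.
- Incremental ratio = (C_SS - C_CBT) / (E_SS - E_CBT).

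If both arms share a change g, so that E_SS = s + g and E_CBT = c + g, then E_SS - E_CBT = s - c. The shared change cancels from the incremental ratio but stays in both average ratios.

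**Step 2: fixed contrast, varying shared change.** Assume costs of 1,500 (Seeking Safety) and 1,000 (CBT), and QALY changes of 0.02 + g and 0.01 + g. The incremental ratio is 500/0.01 = 50,000 throughout.

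| g | Seeking Safety average | CBT average | Lower |
|---|---|---|---|
| 0 | 1,500/0.02 = 75,000 | 1,000/0.01 = 100,000 | Seeking Safety |
| 0.01 | 1,500/0.03 = 50,000 | 1,000/0.02 = 50,000 | tie |
| 0.02 | 1,500/0.04 = 37,500 | 1,000/0.03 = 33,333 | CBT |
| 0.04 | 1,500/0.06 = 25,000 | 1,000/0.05 = 20,000 | CBT |
| 0.08 | 1,500/0.10 = 15,000 | 1,000/0.09 = 11,111 | CBT |

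At an assumed threshold of 80,000 the incremental analysis prefers Seeking Safety for every g, yet the average ratios rank CBT first from g = 0.02 on. At 20,000 it prefers CBT for every g, yet the average ratios rank Seeking Safety first at g = 0.

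**Step 3: acceptability rather than ranking.** Assume 500 euro and 0.020 QALY for CBT, and 650 euro and 0.024 QALY for Seeking Safety. The average ratios are 500/0.020 = 25,000 and 650/0.024 = 27,083, both under an assumed limit of 30,000. The incremental ratio is 150/0.004 = 37,500, above it. The ranking does not change here; what changes is whether Seeking Safety appears affordable.

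**Step 4: a case with no conflict.** Assume costs of 1,200 and 1,000 and QALY changes of 0.05 and 0.04. The average ratios are 24,000 and 25,000, and the incremental ratio is 200/0.01 = 20,000. At thresholds of 50,000 or 80,000 both approaches favour Seeking Safety.

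**Step 5: the ICER as defined.** The plan's expected changes are 4.0 - 1.6 = 2.4 and 4.0 - 2.8 = 1.2 points, a contrast of 2.4 - 1.2 = 1.2. Assume costs of 1,600 and 1,000. The statistic as defined is 600. The ratio is 600/1.2 = 500 per point. If the contrast were half as large, 0.6, the ratio would be 600/0.6 = 1,000 per point, while the statistic as defined would still be 600.

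**The case against.** The strongest reply is that the text is loose, not wrong. The cost-utility sentence says that the quantities can be combined, and it names a single cost per QALY. An incremental ratio also needs each strategy's cost. The section opens by announcing a comparison and has already named the ICER by the time cost-utility is introduced. If the before-after changes were then differenced between arms, shared change would cancel. A condensed article may also leave formulas to the full protocol.

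Part of this stands. A reader might infer that uncontrolled average ratios replace the randomised comparison throughout. The document does not support that for the EuropASI-based analysis: the C/E ratio is followed at once by the ICER between Seeking Safety and CBT, with confidence intervals. A before-after measure is also not a fault in itself.

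The rest does not rescue the cost-utility analysis. The incremental reading is possible but not the natural one. That analysis has its own stated construction, into which the ICER is not carried. The ICER could not supply the missing step in any case, because its definition contains no difference in effect. The article is not merely silent: it prescribes a construction of the benefit and a definition of the ICER, and both are incomplete for the stated aim.

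**Conclusion.** Wrong as written, in two places. The cost-utility analysis, read naturally, gives average ratios that include change common to both arms, and it states neither an incremental cost per QALY nor an interval. The ICER is the right statistic for the EuropASI-based analysis, but its definition lacks the denominator.

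The size in this trial cannot be computed, because no costs, utilities or threshold are given. Under the assumed figures, the order of the average ratios reverses as shared change passes 0.01 QALY while the incremental ratio stays at 50,000. A wrong conclusion is therefore possible, not inevitable, as the case without conflict shows. The finding rests on the natural reading of the cost-utility sentence. It is separate from the direction of the QALY subtraction, which as worded makes a gain negative, and would remain after that was corrected.

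**What to change.** Define both results with the same structure, between randomised arms:

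(mean cost Seeking Safety - mean cost CBT) / (mean effect or QALY Seeking Safety - mean effect or QALY CBT).

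State a confidence interval for each. Estimate the QALY difference with adjustment for the baseline EQ-5D utility. Label any per-arm C/E or per-strategy cost per QALY as descriptive, not as the basis for comparing the treatments.

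The cost is analysis wording only. Treatment costs, the EuropASI and the EQ-5D at baseline and follow-up are already part of the plan.

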## Discussion

This study protocol presents the design of an RCT evaluating the efficacy of the Seeking Safety treatment program in the Netherlands. The goal of the treatment is to reduce substance use and PTSD-related symptoms. Recently Najavits and Hien have summarized the literature on Seeking Safety, which shows consistent improvements when Seeking Safety is used, even among highly complex and severe patients [17]. Therefore it can be expected that an integrated treatment approach for substance use and trauma-related problems can be very effective. Although Seeking Safety has already shown positive results and is considered to be the first choice of evidence-based treatment for comorbid SUD and PTSD, there are several reasons why this RCT should be conducted.

Firstly, the studies from which the results have been used as evidence for the efficacy of Seeking Safety, are largely conducted in the United States. SUD populations in the United States and Europe or the Netherlands are very similar as general characteristics are concerned. However, communication styles differ between countries, because of cultural differences. Also, the Netherlands are known for its liberal policies and views towards several issues, for example drugs. These differences could have influence on the way patients perceive and adhere to Seeking Safety. The treatment uses a book with handouts for patients and guidance for therapists. This book and its handouts have been translated into Dutch in 2010 [35], however, it is important to test the efficacy of the Dutch version for reasons mentioned above. A natural choice for a comparision condition is CBT, which is considered the gold-standard treatment for SUD alone.

Secondly, the majority of studies focused on female populations of SUD patients. While this group in particular may benefit from Seeking Safety, studies on male subpopulations have emerged over the last few years [51]. In general, there are approximately twice as many male patients than female patients in substance use treatment [52] and it is therefore interesting to see what the effect of Seeking Safety is on a population where men are the majority and Seeking Safety groups are mixed-gender. The effect of gender in response to PTSD-focused treatment has not yet been systematically studied [13]. Therefore, in the current study gender will be studied as a possible confounder or modifier of the effect of Seeking Safety.

Thirdly, while previous studies on Seeking Safety have mostly been focused on patients with PTSD, in this study patients will also be included if they have experienced a traumatic event and present with some PTSD symptoms, but not necessary with full-blown PTSD. That way, the possible benefits of this treatment will be available for a substantial larger group of patients. A possible limitation of this procedure is that self-reported PTSD-related symptoms will be used to include patients in the study. Because the sample will consist of SUD patients, a proportion of the symptoms they report, may be due to substance use or withdrawal (e.g. sleep problems, difficulties concentrating). The symptoms of hyperarousal could be independent of any traumatic experience. For the purpose of this study, however, this is not a problem. There may be instances where a patient is included in the study while his symptoms are primarily related to substance use, but we still expect this patients to benefit from Seeking Safety in alleviating his symptoms.

The aim of this RCT is to test the efficacy of Seeking Safety versus CBT in an outpatient population of SUD patients. The design of the study is based on the fact that both Seeking Safety and CBT are evidence-based models, but CBT does not address trauma or PTSD. We expect that a majority of the patients may benefit from a treatment that focuses on both trauma and substance use. If the intervention group is more successful in reducing substance use and PTSD symptoms, it can be argued that Seeking Safety should be offered for patients presenting with trauma issues.

If either treatment proves to be more effective, cost-effectiveness must also be taken into account because scarcity of resources is a permanent feature of mental health care and substance use treatment in particular. It is well documented that patients that experienced trauma are in general higher users of services in the health care system [53]. However, it is difficult to determine for each hospitalization or crisis whether or not underlying PTSD is its direct cause, which makes economic evaluations difficult. Domino et al. [54] attempted to shed light on this subject by analyzing total service costs of women with mental health and substance abuse disorders who have experienced trauma. One group of women was enrolled in an intervention condition, which provided comprehensive, integrated and trauma-informed services. The other women received care-as-usual. The results showed that the intervention modestly improved clinical outcomes, especially drug use and trauma outcomes, and that there were no differences in cost between the intervention and the comparison condition. This provides support for the notion that integrated and trauma-focused interventions can be effective treatments for SUD patients with traumatic experiences, with no significant extra cost.

### Implications for practice

If Seeking Safety turns out to be an effective treatment for the population under study, it could be implemented broadly within the outpatient setting of addiction treatment facilities. Cost-effectiveness analyses will be used to inform policy makers about the possible advantages of implementing Seeking Safety versus CBT.
